### Interventions

#### Standard OD and nutritional care

Both the control and test group will receive standard OD and nutritional care. Standard nutritional care in the current study is in line with the Dutch guidelines for malnutrition [15] and according to the most recent guideline on nutrition in geriatrics of the European Society for Clinical Nutrition and Metabolism (ESPEN) [17]. The control and test group receive dietary counseling and food fortification with enrichment of meals and provision of snacks in between meals. Regular ONS, possibly manually thickened to a safe thickness level, is only provided to the control group residents if food fortification is not sufficient to increase dietary intake and reach nutritional goals. Standard OD care is defined as the routine practice in each nursing home, with references to the Dutch guidelines for OD [16]. 

#### Test product

The test group will receive pre-thickened ONS (the test product) in addition to the standard OD and nutritional care without pre-thickened ONS. The commercially available test product (Nutilis® Complete, Nutricia, Zoetermeer, the Netherlands) is a food for special medical purposes and is provided in 125 mL bottles or 125 g pots. It is intended for dietary management of disease-related malnutrition, and is a high energy, nutritionally complete pre-thickened supplement suitable for patients with swallowing difficulties. Previously conducted clinical and non-clinical studies did not reveal any safety concerns [28–30].

This ONS is pre-thickened to 4 standardized consistencies (i.e. with increasing thickness) that suits the different severity levels of OD, in accordance with the British Dietetic Association (BDA) guidelines [31]. The target viscosity (i.e. thickness defining its resistance to flow) of the pre-thickened ONS is 65, 450, 1200, and 3000 mPa*s at a shear rate of 50 s^− 1^ and a temperature of 20 °C. Table 4 shows an overview of the available flavors, energy density (kCal/100 mL or g), viscosity (mPa.s), BDA stage [31], and corresponding IDDSI level (International Dysphagia Diet Standardization Initiative) for each stage of the pre-thickened ONS [32].

**Table 4 Tab4:** Overview of the test product range

Pre-thickened ONS range	Flavors	Energy density ***(kCal/100 mL or 100 g)***	Viscosity ***(mPa***^a^***s)***	BDA^a^ stage	Corresponding IDDSI^b^ Level
**Drink**	vanilla / strawberry	200	65	n/a	2
**Drink**	vanilla / strawberry / lemon tea / mango passion fruit	245	450	1	3
**Crème**	vanilla / strawberry / chocolate	245	1200	2	3
**Fruit**	strawberry / apple	138	3000	3	4

^a^ Severity levels of OD in accordance with the British Dietetic Association (BDA) guidelines [31]

^b^ Framework of the International Dysphagia Diet Standardization Initiative (IDDSI) [32]

For the test group, a trained SLT and a dietician will provide a patient-tailored recommendation on the safest thickness level of liquids for swallowing and for the amount of nutritional supplementation (≥ 500 kCal or 2–3 units of test product per day).

#### Blinding

Investigating the effect of the test product on top of standard OD and nutritional care precludes a (iso-caloric) control. Therefore, blinding is not possible, and all assessors need to be informed of the intervention plan of the resident. The study coordinator will be involved in the data collection process as well as in data analysis, which also precludes blinded data analysis.

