### Study outcomes

The primary outcome of the DYNAMO study is the difference in body weight change between the control and test group from baseline to final measurements after 12 weeks of intervention.

Secondary outcomes are changes in nutritional intake, HRQoL, OD-specific QoL, and patient compliance to the test product. In addition, a food diary, oxygen saturation, blood nutrient and hydration markers, blood pressure, heart-rate, upper arm and calf circumference, Barthel Index, 7-day activPAL3™, activity log, rating of the test product and dysphagia severity will be assessed.

Any (serious) adverse events ([S]AEs) will be monitored, evaluated, and documented. The relation of (S) AEs to the test product will also be evaluated by a medical doctor. Specific safety outcomes of the current study are: respiratory tract infection, urinary tract infection, dehydration, pressure ulcer, fall incident, all-cause hospitalization, and choking. An overview of study outcomes, corresponding instruments and assessment details can be found in Table 5.

**Table 5 Tab5:** Overview of study outcomes, instruments, and assessment details

	***Outcome***	***Instruments***	***Score***	***Assessment details***
***Primary***	Body Weight	Calibrated lift with integrated scale, mobile chair with integrated scale or wheelchair platform with integrated scale	Body weight weighed to the nearest gram	The resident is in fasting state and preferably dressed in light clothing and without shoes
***Secondary***	Nutritional intake	Standardized three-day food diary and a kitchen scale	Food products weighed to the nearest gram	Food products, leftovers and napkins with spit out food pieces will be weighed by a member of the trained study team
	HRQoL and OD-specific QoL	Standardized questionnaire EQ-5D-5L [33] and VAS: EQ VAS, DSS, DHRQoL [34, 35] and DAS	EQ-5D descriptive system [no problems/slight problems/moderate problems/severe problems/extreme problems] EQ VAS [0–100 score], DSS [0–10 score], DHRQoL [0–10 score], DAS [0–10 score]	Self-assessment or proxy-assessment
	Compliance to test product	Standardized compliance log	Amount of product leftover [no leftover/quarter/half/three quarters/complete leftover]	Filled out by nursing staff
***Exploratory***	ADL	Validated Barthel Index (BI) [36]	0 [dependent] - 20 [independent]	Conducted by a member of the trained study team

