Practical implementations and ethical considerations made it impossible to blind participants and assessors in this study. To the best of our knowledge, we have made every effort to limit the effects of this limitation. Participants are randomly allocated to a treatment arm and intervention procedures (apart from the intervention) are standardized for both treatment groups. The primary measure of the study is an objective and valid measure, all measurements are in line with standard care practice and possible effects will be considered in the analysis of the study outcomes.

This pragmatically controlled study closely reflects standard OD and nutritional care, and study outcomes therefore have real-life applicability. Execution of standard care in the study design also entails a number of limiting factors. Most importantly, standard care may differ slightly between nursing homes, and proper study execution is highly dependent on the engagement of all involved healthcare professionals. Both somatic and psychogeriatric nursing home residents will be included, since OD and malnutrition (risk) are common in both populations. This will result in a highly heterogeneous population, increasing outcome variability. In addition, including incapacitated residents limits some assessments or limits some assessments to be completed by a caretaker. A priori estimation of the inclusion rate is difficult, specifically, the informed consent rate, i.e. the willingness of residents or their legal representatives to participate. Hence, the inclusion rate will be closely monitored.

Dutch nursing homes often comprise of long-term somatic and psychogeriatric wards and short-term rehabilitation wards. Residents at rehabilitation wards follow a rehabilitation trajectory (e.g. after stroke). They are temporarily in need of high intensity care and leave the nursing home after a short period of time. Future studies could also target a group of rehabilitation residents with OD and concurrent malnutrition (risk). In addition, the body of literature on non-institutionalized older populations at risk for OD and malnutrition is poor.

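### Neither reason given under Blinding prevents fitting the primary weight model on coded arms, and Table 5 leaves clothing and shoes to the discretion of a weigher who knows the allocation

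*Protocol article*

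**What the plan says.** The Blinding section of the protocol article reasons in two steps.

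- **Assessors.** The premise is the add-on design: "Investigating the effect of the test product on top of standard OD and nutritional care precludes a (iso-caloric) control". The conclusion is: "Therefore, blinding is not possible, and all assessors need to be informed of the intervention plan of the resident".
- **Analysis.** A different reason is given, one of staffing: "The study coordinator will be involved in the data collection process as well as in data analysis, which also precludes blinded data analysis".

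For the primary outcome, Table 5 (Study outcomes) lists the devices as "Calibrated lift with integrated scale, mobile chair with integrated scale or wheelchair platform with integrated scale". The recording precision is "Body weight weighed to the nearest gram" and the conditions are "The resident is in fasting state and preferably dressed in light clothing and without shoes". Fasting and calibration are stated without qualification. On the natural reading, the preference covers both the light clothing and the absence of shoes.

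The Discussion acknowledges the limitation: "Practical implementations and ethical considerations made it impossible to blind participants and assessors in this study". As mitigation it cites random allocation, standardised procedures, the objectivity of the primary measure, agreement with usual care, and consideration of possible effects in the analysis. It adds, qualified as to the best of the authors' knowledge, that "we have made every effort to limit the effects of this limitation".

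**The concern.** The missing matched control explains why residents and carers know the arm. It does not explain why the person reading the scale must know it, and the article states no such need for weighing. Those who choose product thickness and amount do need to know, but that is a different task. The bar to blinded analysis comes from one person holding two roles. That is an organisational choice and not a property of the intervention.

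This matters because the primary outcome is a change within a resident, for which the Power calculation section expects 1.4 kg. If clothing or shoes differ between baseline and week 12, the difference goes straight into that change. When the weigher knows the arm, such differences need not be balanced between arms. A scale reading is objective, but the choice of what is on the scale is not. Randomisation gives no protection against measurement differences that arise afterwards, and the analysis cannot correct a clothing difference that was not recorded. Recording to the gram adds little if shoes are optional.

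**Working it through.** **Inputs from the Power calculation section:** difference 1.4 kg (1.4 in the test group, 0 in the control group), SD 2.4 kg, alpha 0.05, power 0.90, dropout 20%. Sidedness is not stated.

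**1. The plan's own figure.** n per arm = 2 × (1.960 + 1.282)² × (2.4/1.4)² = 61.8, rounded up to 62. Allowing for dropout, 62/0.8 = 77.5, rounded up to 78. This matches the plan with a two-sided test; a one-sided test gives 51 and then 64, which does not. The sample size is not in question.

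**2. Standard error at the planned size.** SE = 2.4 × √(2/62) = 0.431 kg.

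**3. Systematic weighing difference b between arms, no true effect.** b is an assumption, because the documents give no value. Rejection probability = P(Z > 1.96 − b/SE) + P(Z < −1.96 − b/SE).

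| b (kg) | Share of 1.4 kg | Two-sided type I error |
|---|---|---|
| 0 | 0% | 5.0% |
| 0.1 | 7% | 5.6% |
| 0.2 | 14% | 7.5% |
| 0.3 | 21% | 10.7% |
| 0.5 | 36% | 21.3% |

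For b = 0.3: b/SE = 0.696, so the upper tail beyond 1.264 is 0.103 and the lower tail beyond −2.656 is 0.004, together 0.107.

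**4. Extra random error s per weighing, the same in both arms.** s is also an assumption. A change uses two weighings, so SD of change = √(2.4² + 2s²). Power is for a two-sided t-test with 62 per arm.

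| s (kg) | SD of change (kg) | Power |
|---|---|---|
| 0 | 2.40 | 0.897 |
| 0.5 | 2.50 | 0.871 |
| 0.7 | 2.60 | 0.846 |
| 1.0 | 2.79 | 0.793 |

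The normal approximation gives 0.901 at s = 0 and 0.876 at s = 0.5, so the conclusion does not depend on the method. These losses are on the high side. The SD of 2.4 comes from earlier supplement trials in nursing home residents and may already contain ordinary weighing error.

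**5. Do the stated reasons support the stated conclusions?**

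- No matched control, therefore all assessors informed: this does not follow for weighing.
- Coordinator collects and analyses, therefore no blinded analysis: this follows only if the coordinator works on the original identifiers and arm labels. The Monitoring and data management section already stores encoded data in an eCRF, and Table 5 mentions a data manager. An export with new identifiers and arms coded A/B therefore appears possible.

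**The case against.** The limitation is disclosed and discussed, in a pragmatic trial whose primary outcome is read from a calibrated scale with the resident fasting. No evidence of differential weighing is offered. Random error would cost power without biasing the contrast, and at 0.5 kg per weighing the loss is under 3 percentage points. Coding the arms does not fully mask a coordinator who helped to collect the data. All of this stands, and it keeps the point modest.

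Four stronger readings are tempting, and the documents do not support them:

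- **Open-label treatment is given as the reason for unblinded analysis.** It is not; the coordinator's dual role is.
- **All weighing conditions are optional.** Only clothing and shoes are. Fasting and calibration are stated outright.
- **The article's silence on using one scale per resident, on the compliance cut-off and on the per-protocol definition is a fault.** A condensed article may leave these to the full protocol or analysis plan, which are not shown.
- **Weighing discretion could produce an error as large as the whole 1.4 kg effect.** Nothing in the documents gives such a figure.

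The objection leaves two statements that the article does make: an inference about assessors and analysis that goes further than its reasons, and a clothing and shoe rule that is only a preference.

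**Conclusion.** The point holds in a limited form. The Blinding section closes off masked analysis of the primary outcome for reasons that do not require it, and Table 5 gives an unblinded weigher avoidable discretion over clothing and shoes. This weakens the Discussion's statement about the effort made, but it does not show that the result will be biased.

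Bias is the more important risk. If the arms differed by 0.3 kg through weighing conditions alone, type I error would be about 10.7% instead of 5%. An extra 0.5 kg of random error per weighing would take power from about 0.90 to about 0.87. Both figures assume 62 completers per arm, SD 2.4 kg, a simple comparison of mean changes, and error sizes chosen for illustration. The planned 78 per group stands. This is a cheap improvement, and the State of the study section says that inclusion was still to resume.

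**What to change.** 1. In Table 5 and the weighing instruction, require the same clothing and shoe state at t1, t2 and t3 for each resident, or record and tare any deviation. Use the same scale where feasible, but do not discard a weight when it is not.
2. Keep earlier weights out of sight at weighing.
3. Fit the primary weight model on an export with new resident identifiers and arms coded A/B, prepared by someone other than the coordinator. Freeze the model and analysis sets before the code is broken.
4. Replace the sentence on blinded analysis with one saying that the primary weight analysis is done on coded arms, and that the coordinator's masking is partial because of involvement in data collection.

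**Cost:** wording in the work instruction, one extra field for deviations, and a recoded export. No additional assessor is needed. The only data manager task that the article names is adverse event coding, so responsibility for the export would have to be assigned. Hiding earlier weights does not mask the weigher to the arm. Compliance and per-protocol analyses must wait until the code is broken, because test-product compliance data identify the test arm.

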### Study outcomes

The primary outcome of the DYNAMO study is the difference in body weight change between the control and test group from baseline to final measurements after 12 weeks of intervention.

Secondary outcomes are changes in nutritional intake, HRQoL, OD-specific QoL, and patient compliance to the test product. In addition, a food diary, oxygen saturation, blood nutrient and hydration markers, blood pressure, heart-rate, upper arm and calf circumference, Barthel Index, 7-day activPAL3™, activity log, rating of the test product and dysphagia severity will be assessed.

Any (serious) adverse events ([S]AEs) will be monitored, evaluated, and documented. The relation of (S) AEs to the test product will also be evaluated by a medical doctor. Specific safety outcomes of the current study are: respiratory tract infection, urinary tract infection, dehydration, pressure ulcer, fall incident, all-cause hospitalization, and choking. An overview of study outcomes, corresponding instruments and assessment details can be found in Table 5.

**Table 5 Tab5:** Overview of study outcomes, instruments, and assessment details

	***Outcome***	***Instruments***	***Score***	***Assessment details***
***Primary***	Body Weight	Calibrated lift with integrated scale, mobile chair with integrated scale or wheelchair platform with integrated scale	Body weight weighed to the nearest gram	The resident is in fasting state and preferably dressed in light clothing and without shoes
***Secondary***	Nutritional intake	Standardized three-day food diary and a kitchen scale	Food products weighed to the nearest gram	Food products, leftovers and napkins with spit out food pieces will be weighed by a member of the trained study team
	HRQoL and OD-specific QoL	Standardized questionnaire EQ-5D-5L [33] and VAS: EQ VAS, DSS, DHRQoL [34, 35] and DAS	EQ-5D descriptive system [no problems/slight problems/moderate problems/severe problems/extreme problems] EQ VAS [0–100 score], DSS [0–10 score], DHRQoL [0–10 score], DAS [0–10 score]	Self-assessment or proxy-assessment
	Compliance to test product	Standardized compliance log	Amount of product leftover [no leftover/quarter/half/three quarters/complete leftover]	Filled out by nursing staff
***Exploratory***	ADL	Validated Barthel Index (BI) [36]	0 [dependent] - 20 [independent]	Conducted by a member of the trained study team
	Activity	Activity monitor activPAL3™ (PAL Technologies Ltd., Glasgow, UK) [37, 38] with activity log	Steps [count], upright/sitting/lying position [hours], stepping/standing position [hours]	Applied and completed by a member of the trained study team
	Anthropometrics	Measuring tape	Upper-arm and calf-circumference [cm]	Conducted by a member of the trained study team
	Blood nutritional- and hydration parameters	Laboratory analysis	Osmolality [mOsmol/kg], sodium [mmol/L], vitamin D [nmol/L], vitamin B12 [pmol/L], folate [nmol/L], magnesium [mmol/L], albumin (g/L) and calcium [mmol/L]	Clinical chemical and hematological laboratory of the Zuyderland Hospital (Heerlen-Sittard, the Netherlands)
	Vital signs	Electronic blood pressure monitor	Heart rate [bpm] and systolic and diastolic blood pressure [mmHg]	Conducted by a member of the trained study team
	Oxygen saturation	Oximeter	Oxygen saturation level [%]	Conducted by a member of the trained study team
	Dysphagia severity: swallowing assessment	3-oz WST [26], swallow observation, water thickness test, Modified version of the MISA [27]	Swallow of 3 oz water [positive/negative], descriptive report summary of swallow observation, safest thickness level of liquids for swallowing, completed modified MISA	Conducted by the trained SLT More details in Table 3
	Palatability of the test product	Standardized questionnaire	Taste [1 (poor taste) - 10 (very tasty)], viscosity [too thick/good/too thin], sweetness [too sweet/good/not sweet enough] and swallowing ability [1 (very difficult) - 10 (very easy)]	Self-assessment
***Safety***	(S)AEs	(S) AE forms	MedDRA Medical Coding	Coding will be done by the data manager

*Abbreviations*: EuroQol 5-dimensions 5-level (EQ-5D-5L), Visual Analog Scale (VAS), EUROQoL-VAS (EQ-VAS), Dysphagia Severity Scale (DSS), Dysphagia HRQoL (DHRQoL), Dysphagia-related Anxiety Scale (DAS), 3 oz Water Swallow Test (3-oz WST), McGill Ingestive Skills Assessment (MISA), (Serious) Adverse Event ((S)AE)

### Monitoring and data management

All procedures and persons involved in the collection, handling, and storage of data and documents will be registered in a delegation log. Monitoring will be done by the Clinical Trial Centre Maastricht (CTCM). The data will be handled according to the EU General Data Protection Regulation (GDPR) and the Dutch Act on implementation of the GDPR. Encoded data will be stored in an electronic case report form (eCRF) hosted by an external vendor (Viedoc by PCG Solutions, Uppsala, Sweden).

### Power calculation

Previous clinical trials on ONS in nursing home residents with malnutrition risk have shown a significantly increased body weight in residents that received ONS over a period of three to 6 months compared to residents receiving dietary recommendations or standard OD and nutritional care during this period [21–24]. In a large meta-analysis, Milne et al. (2009) [21] reported a significant weighted mean difference of 2.65% in body weight between patients with mixed geriatric conditions at risk of malnutrition using energy supplementation versus patients without energy supplementation. This equals an effect difference of ~ 1.4 kg for a person weighing 55 kg. This is in line with more recent studies reporting body weight change from baseline of 1.2 kg (SD 2.4) [24], 1.22 kg (SEM 0.45) [23], and 1.4 kg (SD 2.4) [39] after supplementation with ONS (500–600 kcal/day) for 8–12 weeks in nursing home residents with malnutrition risk. Therefore, an increase of 1.4 kg (SD 2.4) in body weight is assumed to be a reasonable expected mean outcome for the current test group. The mean body weight change for the control group is conservatively estimated to remain unchanged despite standard OD and nutritional care. Stange et al. (2013) [24] documented fourteen drop-outs from 87 residents (16%) in the test group. For the current study, we estimate a drop out percentage after randomization of 20%. Based on this a priori estimate with an alpha of 0.05 and 0.90 power, of the required sample size per group (control/ test) was made and totals 78.

### Data analysis

SAS/STAT® Software (by SAS Institute, North Carolina, USA) will be used for analysis of the encrypted data. Descriptive statistics of numerical data will be presented using mean and standard deviation (SD) or median with interquartile range (IQR), and they will be checked visually for normality using histograms and Q-Q plots. Categorical data will be presented in terms of frequencies or percentages. Numerical data of compliance to the test product will also be dichotomized into compliant and not-compliant. Generally, all analyses will be performed according to the intention-to-treat (ITT) principle. Only residents compliant to the intervention will be included in the per protocol analysis, which will be used as a sensitivity analysis for the ITT analyses. Linear mixed models will be performed to check for differences in primary and secondary outcome parameters between the control and the test group at different time-points with correction for baseline differences. A linear mixed model analysis will be used, as this method uses all available data, deals with correlation between repeated measures and assumes missingness to be at random.

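### The per-protocol set is selected on test-product compliance, which exists in one arm only, so it cannot serve as a robustness check on the ITT result

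*Protocol article*

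**What the plan says.** The Data analysis section of the protocol article makes ITT the main principle: "Generally, all analyses will be performed according to the intention-to-treat (ITT) principle". It then adds the per-protocol analysis as a check on ITT: "Only residents compliant to the intervention will be included in the per protocol analysis, which will be used as a sensitivity analysis".

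The compliance variable is introduced in the same section: "Numerical data of compliance to the test product will also be dichotomized into compliant and not-compliant". Study outcomes lists "patient compliance to the test product" among the secondary outcomes. Table 5 has nursing staff record it on a log, as the amount of product left over in five steps. No compliance measure is listed for standard care, or for regular ONS given to controls.

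The Test product section says who can have such a record: "The test group will receive pre-thickened ONS (the test product) in addition to the standard OD and nutritional care without pre-thickened ONS". For controls, Standard OD and nutritional care says that regular ONS "is only provided to the control group residents if food fortification is not sufficient to increase dietary intake and reach nutritional goals".

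**The concern.** Two things are wrong with the stated rule.

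- **It can act on one arm only.** Compliance is recorded only where the test product is given. Test residents who leave product can be removed, but there is no record by which to remove the comparable controls, who would also have left product had they been offered it. The remaining groups are no longer comparable by randomisation. Poor appetite, illness or worse swallowing could lead a resident both to leave product and to lose weight. If so, removing such residents from the test arm alone raises that arm's mean even when the product does nothing.
- **It does not do the job it is given.** The ITT mixed model rests, as the article says, on data being missing at random. Restricting to compliers leaves that assumption untouched and changes the population and the question instead. Agreement between the two analyses would say little about robustness. A favourable per-protocol result beside a weak ITT result could be read as support that it does not provide.

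**Working it through.** **1. The plan's own figure.** Inputs from Power calculation: difference 1.4 kg (control mean change 0), SD 2.4 kg, alpha 0.05, power 0.90, dropout 20%. Sidedness is not stated; two-sided reproduces the result.

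n = 2 × (1.960 + 1.282)² × 2.4² / 1.4² = 61.8, rounded up to 62 evaluable per group. Then 62 / 0.8 = 77.5, rounded up to 78, as stated. The per-protocol set plays no part in this.

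**2. Whom the rule can select.**

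| Element | Test arm | Control arm |
|---|---|---|
| Receives the test product | yes | no |
| Compliance log | yes | none listed |
| Compliant / not-compliant status | yes | undefined |

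Read literally, no control is compliant and there is no comparison. Read so that it works, compliant test residents face all controls.

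**3. What the workable reading could do when the product has no effect.** Let p be the share of the test arm that is compliant, and d the difference in weight change, without any product effect, between those who would comply and those who would not. The whole arm's mean is p × (complier mean) + (1 − p) × (non-complier mean), so keeping compliers only shifts it by

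bias = (1 − p) × d.

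With 62 completers per arm before selection and SD 2.4 in both arms,

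SE = 2.4 × √(1/62 + 1/(62p)).

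The article gives neither p nor d. The values below are assumptions.

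| p | d (kg) | Bias (kg) | Share of 1.4 kg | SE (kg) | Two-sided rejection, nominal 5% |
|---|---|---|---|---|---|
| 0.8 | 0.5 | 0.10 | 7% | 0.457 | 5.5% |
| 0.7 | 1.0 | 0.30 | 21% | 0.475 | 9.7% |
| 0.6 | 1.5 | 0.60 | 43% | 0.498 | 22.6% |

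With d = 0 the bias is 0. With d = −1.0 and p = 0.7 it is −0.30 kg, against the product.

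**4. Second check with a different set-up.** Drop the fraction q of the test arm with the lowest latent compliance, and let rho be the assumed correlation of compliance with weight change. Then

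bias = 2.4 × rho × φ(z_q) / (1 − q).

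For q = 0.3 and rho = 0.3: 2.4 × 0.3 × 0.348 / 0.7 = 0.36 kg. The false-finding column comes from a simulation with 62 per arm.

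| rho | Bias for q = 10% to 40% (kg) | Chance of a false finding for the product, nominal 2.5% |
|---|---|---|
| −0.3 | −0.14 to −0.46 | 1.2% to 0.2% |
| 0 | 0 | about 2.5% |
| 0.1 | 0.05 to 0.15 | 3.1% to 5.0% |
| 0.3 | 0.14 to 0.46 | 4.9% to 14.8% |
| 0.5 | 0.23 to 0.77 | 8.1% to 34.9% |

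Both approaches agree that the sign and size follow from quantities the article does not supply.

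**The case against.** The strongest reply has four parts.

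- **The control-arm rule is not stated.** Nowhere does the article say that all controls are kept. The Interventions section covers standard care as well as the test product, so compliance to the intervention might be meant more broadly. The cut-off and the handling of controls may stand in the full protocol or SAP, which are not shown. This is fair, and neither gap is counted as a fault here. But the rule that is stated relies on a variable that exists in one arm only, and no measure of compliance with standard care is listed that could extend it.
- **The direction is not shown.** A reader might infer that the per-protocol estimate must favour the test product. The documents do not support that. They give no compliance rate and no link between compliance and weight change. The exclusion in Table 2 of residents whose ability or willingness to comply is in doubt could reduce the problem, as could the planned correction for baseline differences. Controls who start regular ONS would tend to narrow the contrast. This stands: the direction is plausible, not established.
- **ITT remains the main analysis.** This also stands. Nothing lets the per-protocol result override it.
- **The label is only terminology.** This does not stand. A sensitivity analysis should vary an assumption of the main analysis, and this one does not.

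It is also tempting to require an instrumental-variable estimate instead, with randomised arm as the instrument. The article's design makes that doubtful. Regular ONS is provided only to controls, so allocation can affect weight by a route other than test-product intake, and the exclusion restriction is strained.

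**Conclusion.** The point holds in limited form. The stated per-protocol rule can in practice select on one arm only, is not protected by randomisation, and does not test any assumption of the ITT model, so it should not be presented as a sensitivity analysis for ITT. The one-arm reading is an inference from where compliance is measured, not a rule the article spells out.

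The 0.1–0.6 kg range is an illustration of what could happen under the assumed p and d, not an estimate for this trial. At the mild end the effect on the error rate is negligible; at the other end it is not. The error rates further assume 62 completers per arm and a common SD of 2.4 kg, a figure the article states for the test group.

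Neither the primary inference nor the sample size is threatened. The text should be corrected, but this is not a fault that must be fixed before the trial can give a valid main result.

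**What to change.** In the Data analysis section:

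1. Define the per-protocol set by protocol deviations that can occur, and be assessed in the same way, in both arms. Examples are a breached eligibility criterion, receipt of the other arm's supplementation, or a weight not taken under the conditions in Table 5.
2. Label the analysis supplementary and delete the clause that makes it a sensitivity analysis for ITT. Even a symmetric per-protocol set is chosen after randomisation.
3. Check the robustness of ITT in all randomised residents, for example by shifting the values assumed for missing week-12 weights away from missing at random by a range of amounts, separately by arm.
4. Keep test-product compliance as the secondary outcome it already is, and describe weight change by compliance within the test arm without a claim about treatment effect.

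An instrumental-variable analysis need not be required.

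The cost is a change of wording and one further analysis of data already being collected. What is lost is a direct comparison labelled as the effect in compliers, which the planned rule could not deliver without bias. State of the study describes inclusion as still to resume, so on the article's account the change can be made before results are known.
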